### Participant Recruitment

Participants will be selected voluntarily. They will be invited to participate in the study through referrals from psychologists and psychiatrists working with individuals on waiting lists at counseling and mental health centers. These include psychological counseling centers at universities and preuniversity institutions. Eligible participants will be identified from the waiting lists of online platforms where they registered for counseling or psychotherapy related to emotional difficulties. Once identified, they will receive an invitation to participate in the research project. After expressing their intent to participate, each participant will receive an informed consent form detailing the study’s specifics. Participants will be formally included in the study upon signing the consent form. Finally, participants will be randomly assigned to one of the proposed psychoemotional support groups. This allocation will be conducted through random assignment, ensuring balanced groups in terms of financial level, type of education, and clinical level of anxiety.

### Eligibility Criteria

#### Inclusion Criteria

According to the Romanian Youth Law Number 350 of July 21, 2006, our research targets the youth age group, which includes adolescents and young adults aged 14 to 35 years. Given that there are specific recommendations regarding participants being aged ≥15 years for using VR software and hardware programs, our program will include adolescents and young adults aged 16 to 35 years. Another essential criterion for inclusion in the research is diagnosis, that is, participants diagnosed with disorders within the anxiety spectrum of mental disorders, particularly performance anxiety, who are capable of understanding and providing consent to participate in the study. Participants lacking full decision-making capacity (eg, those with severe psychotic disorders, schizophrenia, or any other disorder affecting judgment and those who have attempted suicide) are not eligible for participation.

To be eligible, participants must present a clinical or subclinical level of anxiety symptoms, confirmed by medical or psychological evaluation. According to the *Diagnostic and Statistical Manual of Mental Disorders, Fifth Edition* and *the International Classification of Diseases, 11th Revision*, test anxiety can be included within the following broader anxiety disorders: generalized anxiety disorder, social anxiety disorder (SAD; social phobia), or specific phobia. Symptoms include worry on most days, for ≥6 months, related to numerous events such as academic performance, examinations, etc. Anxiety and worry are accompanied by at least 3 of the following symptoms: restlessness, fatigue, difficulty concentrating, irritability, muscle tension, and sleep disturbances. SAD involves fears or anxieties about one or more social situations in which the person is exposed to possible scrutiny by others. For students, this may involve oral examinations or class presentations. Social situations almost always provoke fear or anxiety and are avoided or endured with intense fear or anxiety. Regarding specific phobia, if it centers solely on examinations, then, depending on its intensity and duration, it may constitute a specific phobia. Generally, cases are recorded where fear or anxiety is excessive or disproportionate to the situation, as there is no real threat from the situation itself.

We have also identified the following additional important inclusion criteria: (1) enrollment in an academic center or preuniversity educational institution and placement on the waiting list at psychological counseling centers within universities or preuniversity institutions, (2) the ability to understand all aspects of the study and the preliminary commitment to adhere to its interventions through signing informed consent, and (3) understanding of both Romanian and English.

#### Exclusion Criteria

The research team has identified the following key exclusion criteria that could negatively interfere with and influence the study’s results: (1) lack of consent from a legal representative for minors, undergoing medical treatment, diagnosis of epilepsy, auditory or visual impairments, mobility challenges, spinal disorders, nonclinical levels of anxiety; (2) psychiatric conditions that impair sensory or kinetic abilities required for the intervention procedures; (3) history of cybersickness, photosensitivity crises, or seizures induced by intermittent light stimulation (specific to the VR cohort); and (4) several medical, technological, and biosocial limitations related to exposure to VR techniques. These are detailed in the informed consent provided in Multimedia Appendix 1 for each participant assigned to the *VR* experimental condition. The most important aspects include neurological disorders, visual impairments, vestibular disorders, photosensitivity, cardiovascular issues, pregnancy, severe mental health disorders, technological and environmental limitations, cognitive disorders, impaired judgment, the lack of adherence to past medical or psychological treatments, and language barriers. These criteria are detailed in Multimedia Appendix 1 for each participant in both versions of the informed consent.

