### Procedure

#### Overview

Participants will be invited to attend one of the psychoemotional support groups where they will benefit from either VR-facilitated exposure techniques based on cognitive behavioral intervention modalities or techniques based on the combination of postures (asana), breathing (pranayama), and meditation. Before allocation to the psychoemotional support conditions, each participant will be assessed using a personal data sheet to consider relevant medical, social, and demographic data and exclusion criteria.

This study will use a comprehensive set of preassessment measures to ensure stratified randomization before group allocation. First, measures of both state and trait anxiety are used to ensure participants are grouped appropriately according to their baseline anxiety levels before intervention allocation. Levels of clinical anxiety and emotional regulation mechanisms relevant to anxiety management as well as specific manifestations of performance anxiety will be assessed before the start of the intervention program. Randomization into groups will be done after the initial assessment and will consider an equitable distribution, and the equitable distribution will be considered according to anxiety levels. Given the impact of baseline anxiety levels on treatment effectiveness, a stratified randomization technique is used. This protocol outlines that participants are first stratified based on their anxiety scores and gender before being randomized into the 2 intervention groups. Stratification ensures that individuals with high-trait anxiety and low-trait anxiety are evenly distributed across both treatment groups. Similarly, gender will be controlled to ensure that results are not confounded by gender-related emotional regulation tendencies. This type of stratification minimizes variance and ensures comparable starting conditions for both groups. Finally, this process controls for preexisting differences, leading to stronger statistical effects.

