### Instruments

#### Overview

First of all, participants will complete personal, medical, social, and demographic data sheets to identify aspects that make the volunteer incompatible with participation (ie, country of residence, county or region, gender or sex, level of education, educational attainment, current education, financial situation, marital status, profession, seniority in profession, level of responsibility in the workplace, and physical and psychiatric medical data, eg, current psychiatric diagnosis, undergoing medication, diagnosis of epilepsy, hearing or visual impairment, mobility difficulties, and spinal disorders).

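### The exclusion criteria tie the VR contraindications to the VR arm, while other sections have every exclusion checked before allocation; the passages conflict and, read literally, permit selection in one arm only

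*Protocol article*

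**What the plan says.** Two statements in the protocol article's Exclusion Criteria link VR contraindications to one arm.

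- Criterion 3 is a "history of cybersickness, photosensitivity crises, or seizures induced by intermittent light stimulation (specific to the VR cohort").
- Criterion 4 covers medical, technological and biosocial limits on VR exposure. Of these the article says: "These are detailed in the informed consent provided in Multimedia Appendix 1 for each participant assigned to the" VR condition.

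Other statements point the other way.

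- The same paragraph closes with: "These criteria are detailed in Multimedia Appendix 1 for each participant in both versions of the informed consent".
- Procedure, Overview says that before allocation "each participant will be assessed using a personal data sheet to consider relevant medical, social, and demographic data and exclusion criteria", and that "Randomization into groups will be done after the initial assessment".
- Participant Recruitment says "Participants will be formally included in the study upon signing the consent form", and names random assignment as the step after that.
- Screening describes an enrolment form with questions on mental and physical health. Only those who meet the criteria go on to the initial evaluation.

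Instruments, Overview gives examples of the medical items on the pre-allocation data sheet. They include "diagnosis of epilepsy, hearing or visual impairment, mobility difficulties, and spinal disorders". Cybersickness, photosensitivity, vestibular disorder, cardiovascular problems and pregnancy are not among the examples.

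Data Analysis and Handling Missing Data sets the primary analysis on the intention-to-treat principle, with a per-protocol comparison as a sensitivity check.

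**The concern.** In a two-arm randomised trial, everyone randomised should be eligible for either arm. Before allocation there is no VR cohort, so an exclusion belonging only to that cohort has two ways to operate. It can remove people from the VR arm after randomisation, or it can send people with a contraindication to yoga at the point of allocation. Either way the yoga arm keeps a kind of participant that the VR arm lacks, and the comparison then mixes treatment with selection. Stratifying on anxiety score and gender does not protect against this, because the selection is on other characteristics.

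The consent wording adds to the difficulty. A form intended for people already assigned to VR does not fit a sequence in which consent is signed first. If an arm-specific form were handed over after assignment, people could also decline knowing their arm.

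Staff working from Exclusion Criteria and staff working from Procedure could therefore enrol differently, and selection of this kind cannot be reliably undone in the analysis.

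**Working it through.** **1. The passages side by side**

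| Question | Exclusion Criteria, criteria 3 and 4 | Other text |
|---|---|---|
| Who is covered? | The VR cohort; those assigned to VR | Each participant (Procedure, Overview); both consent versions (end of Exclusion Criteria) |
| When can the criterion act? | Read literally, once the arm is known | Before allocation (Procedure, Overview) |
| When is consent given? | A form for those already assigned to VR | Before random assignment (Participant Recruitment) |
| Does screening cover the VR items? | Not stated | Examples on the data sheet include epilepsy and visual impairment, but not cybersickness, photosensitivity, vestibular, cardiovascular or pregnancy history |

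The first three rows conflict. The fourth leaves the matter open, because the list is introduced as examples.

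**2. The plan's own figure**

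Sample Size Determination gives 30 per group, 80% power and 5% significance, but no effect size or SD, so 30 cannot be reproduced. It can only be inverted. With a two-sided test and the normal approximation, the detectable difference is (1.960 + 0.842) × √(2/30) = 0.72 SD. The point made here does not depend on this figure, which serves only as a yardstick.

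**3. Size if the VR-only wording were acted on by removal**

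The documents give no rates. Assume that a share q of the VR arm is removed and left out of the analysis, and that those removed differ from the rest by δ SD in prognosis. The mean of the full arm is the mean of the remainder plus qδ, so the spurious arm difference is q × δ. Results are for 30 per arm before removal:

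| q (assumed) | VR arm left, 30 × (1 − q) | Bias at δ = 0.25 / 0.5 / 1.0 SD | Power, from 80% |
|---|---|---|---|
| 5% | 28.5 | 0.013 / 0.025 / 0.05 | 79% |
| 10% | 27 | 0.025 / 0.05 / 0.10 | 78% |
| 20% | 24 | 0.05 / 0.10 / 0.20 | 75% |

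The two-sided type I error at q = 10% and δ = 0.5 is found as follows. SE = √(1/30 + 1/27) = 0.265, and 0.05/0.265 = 0.19. Then Φ(0.19 − 1.96) + Φ(−0.19 − 1.96) ≈ 5.4%. In the extreme assumed case (20%, 1.0 SD) it is about 11%.

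**4. Size if people were diverted instead**

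Take the same assumed 10% among 60 participants, all placed in yoga, with the arms kept at 30 each. Then 6 of the 30 yoga participants (20%) and none of the VR participants have a contraindication. The bias is 0.20 × 0.5 = 0.10 SD.

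**The case against.** There is a reasonable innocent reading. The parenthesis on criterion 3 may explain why the criterion exists rather than when or to whom it applies, and it sits in a single list of study exclusions. Procedure, Screening and the closing sentence of Exclusion Criteria all fit the picture of everyone being screened before allocation. The data-sheet items are examples in a condensed article, so the absence of cybersickness or pregnancy does not show that they go unasked. Several criterion 4 items also overlap exclusions that apply to everyone, such as visual impairment, so the VR-only remainder may be small. How and when the two consent versions are used is set out in an appendix that is not shown.

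A reader might go further and infer that the trial will remove VR participants after randomisation, will steer people to yoga, or cannot be analysed by intention to treat. The documents do not support any of these. No passage describes removal for a contraindication. The stated exit route for not completing the programme is a one-month limit, which exists in both arms. Allocation is described as random, and an intention-to-treat analysis would keep such people in their assigned arm if their outcomes are collected.

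These replies weaken the case for actual bias. They do not remove the contradiction: the one-arm wording stands in the eligibility rule itself, and the text does not say which statement governs.

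**Conclusion.** The point holds as an internal contradiction in the eligibility and consent wording that leaves room for selection in one arm. It does not show that randomisation is broken. Confidence is moderate, because several passages favour screening everyone before allocation.

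If the one-arm wording were followed, the likely effect is modest: about 0.05 SD with 10% removed and a 0.5 SD prognostic difference, against a detectable effect of about 0.72 SD. Both inputs are assumptions, and the loss of power is slight. The estimate applies to an analysis that omits those removed. A faithful intention-to-treat analysis with outcomes collected would largely avoid the bias from removal, while the per-protocol comparison would remain exposed. Diversion at allocation would not be repaired by intention to treat.

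The wording should be corrected before enrolment, but this ranks below the defects that would make the trial uninterpretable.

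**What to change.** - Delete the parenthesis that limits criterion 3 to the VR cohort, and the wording that places the criterion 4 limitations with participants assigned to VR.
- State that every exclusion criterion for either intervention is checked in all candidates before randomisation, and make sure the pre-allocation screening covers the VR items.
- State that consent covering both possible assignments is signed before allocation. One merged form would do this. Two versions would also serve if both carry all the criteria and the sequence is kept.
- State that anyone found ineligible after allocation stays in the intention-to-treat set, in the assigned arm.

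The cost is a few lines of eligibility and consent wording and possibly some added screening questions. The one real downside is that candidates with a VR contraindication who could have done yoga are not enrolled, so eligibility narrows slightly. The planned 30 per group does not change.

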### Procedure

#### Overview

Participants will be invited to attend one of the psychoemotional support groups where they will benefit from either VR-facilitated exposure techniques based on cognitive behavioral intervention modalities or techniques based on the combination of postures (asana), breathing (pranayama), and meditation. Before allocation to the psychoemotional support conditions, each participant will be assessed using a personal data sheet to consider relevant medical, social, and demographic data and exclusion criteria.

This study will use a comprehensive set of preassessment measures to ensure stratified randomization before group allocation. First, measures of both state and trait anxiety are used to ensure participants are grouped appropriately according to their baseline anxiety levels before intervention allocation. Levels of clinical anxiety and emotional regulation mechanisms relevant to anxiety management as well as specific manifestations of performance anxiety will be assessed before the start of the intervention program. Randomization into groups will be done after the initial assessment and will consider an equitable distribution, and the equitable distribution will be considered according to anxiety levels. Given the impact of baseline anxiety levels on treatment effectiveness, a stratified randomization technique is used. This protocol outlines that participants are first stratified based on their anxiety scores and gender before being randomized into the 2 intervention groups. Stratification ensures that individuals with high-trait anxiety and low-trait anxiety are evenly distributed across both treatment groups. Similarly, gender will be controlled to ensure that results are not confounded by gender-related emotional regulation tendencies. This type of stratification minimizes variance and ensures comparable starting conditions for both groups. Finally, this process controls for preexisting differences, leading to stronger statistical effects.

The participants will then start the psychoemotional support program and complete an anxiety level assessment at the end of each intervention session. At the end of the program, participants will complete the anxiety questionnaire again, along with an instrument assessing their comfort, discomfort, and the quality of the specific intervention techniques. To evaluate manifestations of performance anxiety, correlations between clinical anxiety and academic anxiety will be checked to indicate the strength and significance of their relationship. Details about the implementation of the techniques are presented in Table 1.

**Table 1 table1:** Overview of intervention components for virtual reality (VR)–assisted cognitive behavioral therapy (VR-CBT) and yoga-based interventions.

Intervention and phase		Session components	Duration
**VR-CBT**			
	Introduction and familiarization (sessions 1-2)	Psychoeducation, familiarization with VR equipment, and guided relaxation exercises	20-30 min per session
	Active exposure (sessions 3-8)	Exposure to anxiety-inducing VR scenarios (eg, virtual presentations), cognitive restructuring, and relaxation	20-30 min per session
	Evaluation and feedback (session 9)	Review of selected VR scenario, QoLI^a^, debriefing, and feedback	20-30 min

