Previous research on VR-assisted CBT (VR-CBT) has predominantly focused on its efficacy in treating social anxiety, phobias, and generalized anxiety, often comparing it to passive relaxation or mindfulness-based interventions. However, these comparisons have largely assessed meditation, guided breathing, and progressive muscle relaxation without incorporating structured movement-based interventions such as yoga. This study addresses a critical gap by directly comparing the effects of VR-CBT with yoga, which extends beyond passive relaxation through the integration of physical postures (asanas), controlled breathing techniques (pranayama), and ethical self-discipline (Yama and Niyama). Unlike meditation alone, yoga actively engages both the body and mind, promoting physiological regulation of stress through autonomic nervous system modulation and improving emotional regulation via structured movement and breathwork. Previous studies have shown that VR-CBT provides rapid symptom relief through immersive exposure and cognitive restructuring, while meditation and relaxation techniques tend to cultivate mindfulness without the added physical benefits of yoga. By assessing yoga as a distinct intervention, this study aims to determine whether its multimodal approach leads to more sustainable long-term reductions in performance anxiety compared to the short-term but potentially more immediate effects of VR-CBT. The findings will offer new insights into the comparative efficacy of digital and traditional mind-body interventions for academic anxiety, contributing to the development of more tailored therapeutic strategies.

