**Yoga-based intervention**			
	Yoga practices (sessions 1-10)	Body postures (asanas), breathing techniques (pranayama), meditation, and relaxation exercises	60-90 min per session
	Final assessment (after the intervention)	QoLI, and self-report feedback on intervention experience	60 min

^a^QoLI: Quality of Life Inventory.

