### VR Cognitive Behavioral Intervention and Theoretical Background

The psychoemotional support intervention, facilitated by VR exposure techniques (6-10 sessions), uses Guided Meditation VR software and stand-alone Oculus Quest 2 and HTC Vive Flow hardware for alleviating performance anxiety. These consist of approximately 6 to 10 sessions of 20 to 30 minutes each of psychoemotional support based on cognitive behavioral techniques and integrative psychotherapy (with extension to a maximum of 1 h, if necessary). They will be carried out over a period of 2 weeks, up to a maximum of 1 month if it is not possible to organize the sessions in optimal conditions. After 1 month, the participants are reported as having withdrawn (in case of a request from the participants) or dropped out of the psychoemotional support program. The initial sessions (1-2 sessions) are designed for psychological assessment, psychoeducation, and familiarization with VR exposure techniques. In the next 2 to 3 sessions, different VR scenarios are tested to find a comfortable virtual environment for each patient. We test if patients agree that they are present in that generated virtual environment in a manner comparable to exposure in a natural environment (eg, a walk by the beach, in a forest, or an underwater itinerary). At this stage, subsequent exposure techniques will be developed using a combination of cognitive restructuring and relaxation methods, aimed at familiarizing participants with the technology and ensuring a pleasant experience. The next 1 to 2 sessions will continue with exercises already chosen, based on cognitive restructuring techniques combined with relaxation techniques. The last session is designed to review one of the exercises, assessing the quality of the technique and offering suggestions for improvement by going through a set of questions (eg, QoL through the QoL questionnaire). Each session concludes with a brief clinical assessment of anxiety using the State-Trait Anxiety Inventory (STAI) tool. Specific manifestations of performance anxiety are assessed.

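### The VR arm is described in two incompatible ways: anxiety-inducing exposure in a 9-session course (Table 1), or comfortable scenes in phases that add to 5–8 sessions (intervention text)

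*Protocol article*

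**What the plan says.** The overview of the Procedure section refers the reader to Table 1 for how the techniques are implemented. Table 1 sets out the VR-CBT arm in three phases: two introductory sessions (1–2), a block headed "Active exposure (sessions 3-8"), and one evaluation session (9). The content of the middle block is "Exposure to anxiety-inducing VR scenarios (eg, virtual presentations), cognitive restructuring, and relaxation".

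The section VR Cognitive Behavioral Intervention and Theoretical Background describes the same arm differently. It states a total of about 6 to 10 sessions and says that the intervention "uses Guided Meditation VR software and stand-alone Oculus Quest 2 and HTC Vive Flow hardware". After 1–2 opening sessions come 2–3 sessions in which "different VR scenarios are tested to find a comfortable virtual environment for each patient"; the examples are a beach walk, a forest and an underwater route. The techniques developed at that stage combine cognitive restructuring with relaxation and are "aimed at familiarizing participants with the technology and ensuring a pleasant experience". The next 1–2 sessions carry on with the exercises already selected, and a last session reviews one of them. The section uses the terms exposure and cognitive restructuring. Its only mention of performance anxiety within the course of sessions is that its manifestations are assessed; no presentation, examination or other performance scene appears.

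For yoga, Table 1 lists sessions 1–10, and the yoga section gives 6 to 10.

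**The concern.** The Goal of This Research section asks how VR-facilitated exposure based on cognitive behavioral intervention compares with yoga. It expects VR to do more for state anxiety and yoga to do more for trait anxiety. Under Table 1, the trial sets confrontation with feared performance situations against a mind-body practice. Under the intervention text, the VR arm is largely relaxation with cognitive restructuring in agreeable scenes, set against a yoga arm that also contains meditation and relaxation. These are different contrasts, and the same result would be read differently under each.

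State anxiety is the most exposed. STAI-Y1 is part of the primary outcome, and the STAI is also given at the close of each VR session. A state score taken just after a calming scene does not carry the same meaning as one taken just after an anxiety-inducing presentation.

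The count matters less but has practical consequences. The article plans a per-protocol comparison, classes participants not finished within a month as withdrawn or dropped out, and provides for adherence checks and audits. Each of these needs a single description of a complete course.

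**Working it through.** This check sets passages side by side and adds session counts. No sample-size formula is involved.

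**Content**

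| Element | Table 1 | VR intervention section |
|---|---|---|
| Software | not stated | guided-meditation software |
| Scenes | anxiety-inducing, for example virtual presentations | comfortable, for example beach, forest, underwater |
| Stated aim of the middle sessions | active exposure | familiarization and a pleasant experience, then the same exercises continued |
| Performance scene named | yes | no |
| Cognitive restructuring and relaxation | yes | yes |

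The last row is common ground. The scene type and the stated aim differ.

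**Session counts**

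Inputs from the VR intervention section: opening phase 1–2, scenario testing 2–3, continuation 1–2, last session 1.

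- Minimum: 1 + 2 + 1 + 1 = 5.
- Maximum: 2 + 3 + 2 + 1 = 8.
- Stated total in the same section: 6–10. The phases fall 1 short at the lower end (6 − 5) and 2 short at the upper end (10 − 8), so the stated range is not reproduced.

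Inputs from Table 1: sessions 1–2 (2), sessions 3–8 (6), session 9 (1).

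- Total: 2 + 6 + 1 = 9. Even with every text phase at its upper limit, the sum is 8 and does not reach 9.

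Sessions between the introduction and the final review:

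- Text: 2 + 1 = 3 up to 3 + 2 = 5.
- Table 1: 6.

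**Yoga**

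Table 1's 10 sessions lie inside the 6–10 of the yoga section. The two places differ only in giving a fixed number or a range.

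**The case against.** The strongest reply is that the two accounts share more than they dispute. The text keeps exposure techniques, cognitive restructuring and relaxation, the same elements as Table 1's active phase. The beach, forest and underwater scenes are only examples, attached to the step that tests scenarios and presence. Performance scenes are not ruled out, and the theoretical background in the same section describes VR-CBT as graded contact with anxiety-inducing scenarios. Table 1 is captioned as an overview, its 9 sessions lie within the stated approximate range of 6–10, and the sample-size section says that the intervention is adapted to individual needs.

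Much of this stands, and it limits the point. A reader might infer that the VR arm has no definition at all. The documents do not support that: the arm has two descriptions that share some components. A reader might also infer that the effect estimate would be meaningless. It would not: randomization still gives a valid comparison of the arms as delivered, and the difficulty lies in naming and interpreting them. That facilitators would in fact deliver a mixture is conjecture, because manuals may exist in a fuller protocol.

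Three further inferences fail.

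- **Already studied.** One might say that relaxation-type VR against yoga repeats earlier work. The Background says of VR-CBT research that it was "often comparing it to passive relaxation or mindfulness-based interventions". There, relaxation is the comparator of VR-CBT, and the next sentence says that movement-based practice such as yoga was not included.
- **Contact time.** The text ranges suggest a threefold imbalance: VR 6 × 20 = 120 to 10 × 30 = 300 minutes, yoga 6 × 60 = 360 to 10 × 90 = 900. But VR sessions may be extended to 1 hour. At the upper end that gives 10 × 60 = 600 minutes and a ratio of 900/600 = 1.5. Unequal session lengths are in any case openly stated and contradict nothing.
- **Yoga count.** Ten lies within 6–10, so this is an imprecision.

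The reply does not remove the core. The sessions after scenario testing continue the exercises already selected, so the text has no later step at which anxiety-inducing scenes enter. Adaptation to the individual does not explain why the listed phases cannot reach the upper end of the section's own total. Nor is this a matter of condensation, since both descriptions stand in the same article.

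**Conclusion.** The point holds as an internal contradiction about the VR arm. On content, Table 1 specifies six sessions of anxiety-inducing exposure with a performance example, while the intervention text specifies comfortable scenes that are then continued and names no performance scene. On count, the text's phases give 5–8 sessions, against its own 6–10 and Table 1's 9, and the middle block is 3–5 sessions against 6. The content conflict is the more serious, because it decides whether the trial addresses its stated question about VR exposure. The count conflict alone would be a wording repair.

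This reading assumes that the four phases listed in the text are meant to make up the whole course and that the last session is a single session, as written. The effect on the size of any treatment difference cannot be quantified from the article.

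**What to change.** Before enrolment:

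1. Reconcile Table 1 with the VR intervention section so that scenario type, phase breakdown and session total agree in both places. The investigators must decide which content and count apply; this review takes no position.
2. State in both Table 1 and the yoga section whether the number of yoga sessions is fixed or a range.
3. Make the name of the VR arm, the stated goal and the planned conclusions match the content that is kept.
4. Record the number of sessions each participant receives, so that the course delivered can be described alongside the results.

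The cost is protocol wording, alignment of facilitator materials and a simple session log, with no additional participants. It should come first because a mixture of delivered versions could not be separated afterwards in the analysis.
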